### Participant timeline {13}

The participant timeline is described in the flow chart (Fig. 1).

**Fig. 1 Fig1:**
[figure not shown]
Flow chart demonstrating the participant timeline

The schedules of biological procedures, assessments and samples are summarized in the following tables (Tables 1 and 2).

**Table 1 Tab1:** Schedule of procedures

Variables	Timings (day)												
	1	2	3	4	5	6	7	8	9	10	11	21+/−2	M3
**Informed consent**	X												
**Demographics**	X												
**Medical history**	X												
**Signs and symptoms**	X	X	X	X am							X	X	
**Vital signs**	X	X	X	X							X	X	
**Doses administered at CSB (am and pm)**	XX	XX	XX	X am									
**Doses administered at home (am and pm)**				X pm	XX	XX	XX	XX	XX	XX			
**Adverse events**	X	X	X	X							X	X	
**Bubo size and pain score**	X			X							X	X	

Assessments will be done within 24 h of enrolment, depending on the time of admission

*M3* 3 months after inclusion

**Table 2 Tab2:** Assessment schedule

Variables	Timing (days)												
	1	2	3	4	5	6	7	8	9	10	11	21+/−2	M3
**RDT Bubo/sputum**	X												
**PCR Bubo/sputum**	X												
**Bubo/sputum culture**	X												
**Plague serology**	X										X	X	X*
**Malaria Ag**	X												

*Only subjects with positive serology on the 21st day will participate in this follow-up

The conduct of the study is described in Fig. 2.

**Fig. 2 Fig2:**
[figure not shown]
Conduct of the study

The maximum volume of blood to be collected during the entire duration of the study (3 months) for confirmed cases with a positive serology at D21 will be 8 ml for children and 16 ml for adults.

### Sample size {14}

Assuming that 90% of individuals receiving streptomycin plus ciprofloxacin (control treatment) meet the primary endpoint definition of therapeutic response on day 11, 190 confirmed/probable bubonic plague patients (95 per group) would be required to have 90% power to demonstrate the non-inferiority of ciprofloxacin treatment compared to streptomycin plus ciprofloxacin, with a 15% non-inferiority margin and a one-sided confidence interval of 2.5%. This calculation takes into account a 10% loss to follow-up rate by the end of treatment. In total, approximately 600 suspect patients will have to be recruited to obtain a sample size of 190 confirmed/probable patients.

Table 3 shows the total sample sizes (both arms) for confirmed/probable bubonic cases to demonstrate non-inferiority with 90% power, 2.5% one-sided test and assuming 10% loss to follow up, based on treatment success in the streptomycin and ciprofloxacin group and the non-inferiority margin.

**Table 3 Tab3:** Total sample sizes (both arms) for confirmed/probable bubonic cases

Therapeutic response*	Margin (%), unilateral confidence interval of 2.5%, loss of 10%, power 90%										
	5	6	7	8	9	10	11	12	13	14	15
**0.95**	890	618	454	348	276	224	186	156	134	114	100
**0.90**	1684	1170	858	658	520	424	350	294	250	216	**190**
**0.85**	2384	1656	1216	932	736	596	494	416	354	306	268
**0.80**	2990	2076	1528	1170	926	750	618	520	444	384	334
**0.75**	3506	2434	1790	1370	1084	878	726	610	520	450	392

*Proportion of “therapeutic response” in the streptomycin and ciprofloxacin group

### Recruitment {15}

Sites will be geographically spread throughout pre-identified districts which report a high incidence of plague. Further districts may be included later in the trial in the event that they also report a high incidence of plague.

Whilst it is the responsibility of site medical staff to assess eligibility and enrol patients, the clinical study nurse, who will be based within the district, will review and verify the eligibility of each patient. Community health workers, who will cover a wider geographical area within the districts and reach more remote communities, will also be trained on the protocol and refer suspected cases of plague to the local CSBs.

#### Community engagement and outreach

Outreach teams will disseminate health promotion messages to local health authorities and communities about plague (i.e. signs and symptoms), as well as the background and objectives of the trial.

Community health workers will also raise awareness about going to health centres in the event of suspected plague.

A social science component will address the practical aspects and uptake of the trial that may be affected by the perception of the trial design by both heath care professionals and patients.

## Assignment of interventions: allocation

### Sequence generation {16a}

Bubonic or pneumonic plague patients will be randomized using a computer-generated randomization sequence generated from the master list, stratified by health facility and clinical form of the disease (bubonic or pneumonic plague).

### Concealment mechanism {16b}

The allocation sequence was compiled in STATA in a way that is unpredictable and unreproducible. A copy of the STATA randomization code file used to compile the list can be requested from the trial statistician. The trial statistician will have access and be responsible for the generation and quality assurance of the randomization list. This also includes any changes and/or extensions to the randomization list and date/s when new any treatment groups become effective.

### Implementation {16c}

The trial statistician has generated the allocation sequence.

The doctor in-charge at the CSB will confirm the eligibility of patients with the support of the clinical study nurse. To randomize patients, the doctor in-charge will call the clinical research associate who will randomize the patient on the site’s behalf, informing the site of the treatment allocation over the phone. Contingency plans have been put in place to ensure randomization can take place in the event of internet or mobile signal outage.

## Assignment of interventions: blinding

### Who will be blinded {17a}

Blinding of patients and the trial team to treatment allocation will not be possible due to the different administration routes of the treatments.

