#### Duration of therapy

The study drugs will be administered for a total of 10 days. After 10 days, the decision whether to continue therapy will be at the treating physician’s discretion.

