### Outcomes {12}

#### Primary endpoint

The proportion of patients with bubonic plague with a therapeutic response (assessed on D11). Therapeutic response is defined as follows for subjects with a visible and measurable bubo:
AliveResolution of fever (uncorrected axillary temperature < 37.5 °C)A ≥ 25% decrease in bubo size (in the case of multiple buboes, the largest bubo)Has not received alternative treatment for plagueNo clinical decision to continue anti-plague antibiotics beyond day 10

For patients with small buboes that are palpable but not measurable:
AliveAbsence of fever (uncorrected axillary temperature < 37.5 °C)Bubo has not enlargedHas not received alternative treatment for plagueNo clinical decision to continue anti-plague antibiotics beyond day 10

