### Procedure for unblinding if needed {17b}

Not applicable—this is not a blinded trial.

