### Data management {19}

All data will be recorded on a paper CRF by clinical study nurses at each study site using a combination of data directly from patients, patient records and laboratory results. The clinical study nurses will then transfer the data from the paper CRF to a RedCap database (version 8.5.17), which will be located centrally at IPM with restricted access. Data queries will be automatically generated by RedCap and transferred to the operational teams in the districts for data quality monitoring as the study progresses. Data monitoring will be conducted on a regular basis as defined in the monitoring plan. The final database will be transferred to Oxford University.

A statistical analysis plan will be prepared prior to the receipt of any data by the trial statistician.

The management, reporting processes and data storage within this trial will comply with the requirements of European Directive (reference 2016/679, “GDPR Directive”) on data protection which is translated into English law by the “Data Protection Act” of May 2018, the Good Clinical Practices of the GCP-ICH, and CIOMS.

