## Oversight and monitoring

### Composition of the coordinating centre and trial steering committee {5d}

IPM will jointly coordinate the trial with the sponsor, the University of Oxford.

As well as a central trial coordination team to coordinate the day-to-day activities of the trial, IPM will deploy one clinical research associate and two clinical study nurses to each district who will assist the sites with the recruitment, data collection and conduct monitoring activities. IPM will also be primarily responsible for data management but supported by the University of Oxford.

The University of Oxford will coordinate the sponsor activities, coordinate the trial committees and provide day-to-day management and oversight of the trial.

The TOC is coordinated by the University of Oxford and is composed of members from each of the study partners to review the operational management of the trial and discuss any urgent matters related to trial conduct as and when they arise. The group meets on a weekly basis to discuss study progress.

The Trial Steering Committee provides overall supervision for the trial on behalf of the trial sponsor and to ensure that the study/trial is conducted according to the guidelines for Good Clinical Practice (GCP) and all relevant regulations and local policies.

A Data Safety Monitoring Board has also been established to maintain oversight of patient safety and data integrity within the trial.

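### Different routes do not explain an unmasked day 11 calliper reading, and the composite also counts a discretionary decision by a physician who knows the arm

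*Protocol article*

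**What the plan says.** Section 17a of the protocol article states: "Blinding of patients and the trial team to treatment allocation will not be possible due to the different administration routes of the treatments". Section 17b confirms that "this is not a blinded trial". Under Implementation (16c), the clinical research associate randomizes on the site's behalf, "informing the site of the treatment allocation over the phone".

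The primary endpoint (Outcomes, section 12) is a day 11 composite of five criteria. Two are survival and a temperature below the threshold. The third is a bubo criterion: "A ≥ 25% decrease in bubo size" where the bubo can be measured, and absence of enlargement where it can only be felt. The last two are that no alternative plague treatment was given and that no decision was made to prolong antibiotics past day 10. On that last item, Duration of therapy says that "the decision whether to continue therapy will be at the treating physician", that is, at his or her discretion.

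Under Data management (19), "All data will be recorded on a paper CRF by clinical study nurses at each study site". Section 5d adds that "IPM will deploy one clinical research associate and two clinical study nurses to each district".

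**The concern.** An open-label trial can still protect the part of its endpoint that is read with an instrument. Here one reason, the different routes, is given for leaving the whole team unmasked, and it does not reach a calliper reading taken after both arms have spent a week on the same drug. A reader who knows the arm and has the baseline value at hand knows which reading would make the patient a responder.

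The continuation decision raises a separate problem. It is made by someone who knows the arm, and it alone can turn a recovered patient into a failure. The article gives motives in both directions. The Objectives describe the two regimens as third-line (ciprofloxacin alone) and first-line in national guidance, which could make a physician readier to prolong treatment after monotherapy. The Study rationale sees no reason to expect a difference in effectiveness and expects ciprofloxacin to become the first choice if it is shown to work.

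Bias against ciprofloxacin costs power. Bias in its favour raises the chance of a false claim of non-inferiority. The composite result alone cannot show which has occurred.

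**Working it through.** **Does the stated reason reach day 11?**

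- Days 1 to 3: control patients receive intramuscular streptomycin and the other arm receives ciprofloxacin (Intervention description; Route of administration). The routes differ.
- Days 4 to 10: both bubonic arms receive ciprofloxacin, orally unless one of the listed conditions applies. The routes do not differ by arm.
- Day 11: dosing is over and the endpoint is assessed.
- Patients with mixed bubonic and pneumonic disease follow the pneumonic schedule, with five days of streptomycin in the control arm. They too have had no injection for several days by day 11.

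The route difference therefore explains why patients and treating staff know the arm, and they still know it on day 11. It does not explain why the calliper reading must be taken with knowledge of the arm or of the earlier values.

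**How much room is there for judgement?** The pilot (section 18a) accepted a difference of up to 25% between two nurses, the same size as the response threshold. It tested agreement between observers and did not address masking.

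**The plan's own sample size.** Inputs from section 14: response 0.90 in both arms, margin 0.15, one-sided 2.5%, power 90%, loss 10%.

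- n per arm = 2 × 0.90 × 0.10 × (1.960 + 1.282)² / 0.15² = 84.06, rounded up to 85
- 85 / 0.90 = 94.4, rounded up to 95 per arm, 190 in total

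This reproduces the stated 190.

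**Illustrative effect of a shift b.** The values of b are assumptions, as the article gives no figure. The normal approximation with unpooled variance is used, with 85 evaluable per arm and control at 0.90.

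- Bias against ciprofloxacin, arms truly equal: p = 0.90 − b; power = Φ[(0.15 − b)/SE − 1.96]
- Bias in its favour, truly 15 points worse: p = 0.75 + b; error = Φ[b/SE − 1.96]
- SE = √{[0.09 + p(1 − p)]/85}

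Worked for b = 0.05:

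- Against: SE = √[(0.09 + 0.1275)/85] = 0.0506; 0.10/0.0506 − 1.96 = 0.017; power 0.507.
- In favour: SE = √[(0.09 + 0.16)/85] = 0.0542; 0.05/0.0542 − 1.96 = −1.04; error 0.150.

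| Shift b | Patients in one arm (85 × b) | Power, bias against | One-sided error, bias in favour |
|---|---|---|---|
| 0 | 0 | 90.3% | 2.5% |
| 2 points | 1.7 | 77.3% | 5.4% |
| 3 points | 2.5 | 69.0% | 7.8% |
| 5 points | 4.2 | 50.7% | 15.0% |

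These figures apply to the composite as a whole. They do not show how much of any shift would come from the bubo reading, or how much masking it would recover.

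**The case against.** The strongest reply is that the reason is correct for the people it names. Treating staff give the injections or are told the allocation by phone, and study nurses share in patient management, so their knowledge does not lapse on day 4. This stands. A reader might infer that the route argument fails altogether, or that the trial could have been blinded. The article does not support that.

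A second reply is practical. Fifty health centres in five districts make about ten centres for each pair of nurses, who also support recruitment, verify eligibility and record the data. The Discussion describes scattered sites with difficult access. Requiring a different nurse on day 11 would be a real burden and would add inter-observer noise, for which the pilot tolerated up to 25%. Patients can also reveal whether they were injected. This stands against any rule that the reader must be changed, but not against concealing earlier values from whoever reads.

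Third, hiding the baseline cannot work for buboes that are palpable but not measurable, because absence of enlargement is a judgement against baseline. This stands, and those patients must be exempt.

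Fourth, an analysis restricted to survival, fever and bubo size would count a patient who failed, was switched and then recovered as a responder, which favours non-inferiority. This stands, so alternative treatment must remain a failure.

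Fifth, component analyses commonly belong in the SAP, which is not shown. The statement in section 20b that no additional analyses are planned appears under a heading about subgroup-type analyses. It would be wrong to infer that a component breakdown is missing from the plan. It is proposed here as a complement to the composite.

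Callipers, training, the concordance pilot and monitoring focused on the primary endpoint do limit measurement error, though none of them masks the reading.

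**Conclusion.** The point holds within limits. The stated reason for no masking is sound for patients and treating staff but does not extend to the day 11 calliper reading. The composite also includes a continuation decision made at discretion by a physician who knows the arm. Survival is objective and temperature largely so, so the concern lies with the remaining components.

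The size and direction of any bias are unknown. Under assumed shifts of 2 to 5 points, roughly two to four patients in one arm, power falls from 90% to about 77% to 51%, or the one-sided error rises from 2.5% to about 5% to 15%. These figures show how sensitive the conclusion is. They do not show that bias of this size will occur, and a reader should not infer that the trial is tilted toward either arm. This is an inexpensive improvement worth making to an openly declared open-label trial. The planned sample size is unaffected.

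**What to change.** 1. **Plans for assessment and collection of outcomes (18a).** For measurable buboes, have the day 11 calliper axes recorded without sight of the day 1 and day 4 values. Give the reader only the location of the index bubo, compute the percentage change centrally, and record whether the reader knew the allocation. Use a reader not involved in the patient's care only where this needs no extra travel or staff. Exempt non-measurable buboes.

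2. **Primary endpoint analysis (20a), or the SAP.** Tabulate failures by component and arm. Beside the composite, add one supportive analysis against −0.15 that omits only the decision to continue antibiotics and keeps alternative treatment as failure. The composite stays primary.

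The cost is a CRF change and a little more analysis, with no additional patients or staff and no change to any clinical rule. Two gaps remain. Day 4 readings, which can settle the outcome for patients lost before day 11 (section 20c), stay unmasked. So do the discretionary decisions themselves: the table and the supportive analysis show how far the conclusion depends on the continuation decision but do not remove its influence.

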### Procedure for unblinding if needed {17b}

Not applicable—this is not a blinded trial.

## Data collection and management

### Plans for assessment and collection of outcomes {18a}

Data will be collected on a paper CRF and then transferred on to a RedCap database for assessment. Automatic validations on RedCap will assess data for completeness and accuracy. A thorough assessment of data accuracy will be performed via regular monitoring activities with a focus on primary endpoint data and safety data, as described in the trial’s monitoring plan.

To validate the methods used to achieve the primary endpoint (% decrease in bubo size), a pilot study and training exercise were conducted ahead of activation in which multiple bubo (real and artificial) measurements were taken using digital callipers (and ultrasound during the pilot). The data were used to assess the concordance of measurements being taken by independent observers. The percentage difference between the sum of the longest and shortest axes of measurements taken by two different clinical study nurse was calculated with an acceptable margin of 25%. The results showed there was less than 25% difference between each measurement.

### Plans to promote participant retention and complete follow-up {18b}

Patients will be provided with a mobile phone upon discharge from the treating centre to optimize retention during follow-up. Community health workers will also assist with reminding patients about their upcoming follow-up visits.

If a patient chooses to withdraw from trial treatment (or the treating clinician believes this is in the best interest of the patient), the patient will continue to receive the standard of care treatment at the discretion of their treating clinician, regardless of the treatment arm to which the patient was randomized. The patient will remain within the trial for the purpose of follow-up, data collection, monitoring and data analysis. Healthcare personnel should explain the importance of allowing existing data to be used, as well as the importance of remaining within the trial for follow-up data collection. If it is not possible to collect further data from the patient at the scheduled trial visits, routine data should be collected via the patients’ medical records.

If a patient withdraws their consent to participate in the trial, data and sample collection will cease and only data up to the point of withdrawal will be used for analysis.

### Data management {19}

All data will be recorded on a paper CRF by clinical study nurses at each study site using a combination of data directly from patients, patient records and laboratory results. The clinical study nurses will then transfer the data from the paper CRF to a RedCap database (version 8.5.17), which will be located centrally at IPM with restricted access. Data queries will be automatically generated by RedCap and transferred to the operational teams in the districts for data quality monitoring as the study progresses. Data monitoring will be conducted on a regular basis as defined in the monitoring plan. The final database will be transferred to Oxford University.

A statistical analysis plan will be prepared prior to the receipt of any data by the trial statistician.

The management, reporting processes and data storage within this trial will comply with the requirements of European Directive (reference 2016/679, “GDPR Directive”) on data protection which is translated into English law by the “Data Protection Act” of May 2018, the Good Clinical Practices of the GCP-ICH, and CIOMS.

### Confidentiality {27}

All the systems used for data management comply with the GCP-ICH and CIOMS recommendations as well as the European Directive (reference 2016/679, “GDPR Directive”) on the protection of personal data, which is translated into English law by the “Data Protection Act” of May 2018.

#### Participant confidentiality

Trial staff will ensure that the participants’ anonymity is maintained. All trial documents will be labelled only with a trial identification number. Trial samples will be labelled only with a trial ID. Routine bubo and sputum samples, which will be analyzed as part of the trial, will be transferred to IPM as per the standard transfer process. The routine samples taken from trial patients will be labelled with a collection label which will not contain a patient trial identifier. A separate letter will be sent to IPM containing anonymised collection information and the patient’s trial ID. This will be used to ensure the results of sample testing from the lab are collected for the trial without compromising the patient’s anonymity.

For the purpose of ensuring data integrity and to facilitate quality assurance, study records will be linked to clinic files, which include the patient’s name and other identifying information. Participants’ names will be recorded confidentially at site in a protected master list at the time of enrolment to allow for their identification at follow-up visits. The master list will not be shared with any other parties involved or not involved in the trial.

All trial data will be stored in a secure database only accessible to trial staff. Only members of the trial team who have completed appropriate data protection training will have access to the password-protected computer where trial data is stored. Study sponsors and health authorities will be given controlled access for the purpose of audit. After the conclusion of the project, data will be removed from the computers and stored in a secure location. Any scientific publications or reports will not identify any patient by name or initials.

